#### Secondary measures and covariates

The following are the secondary measures and covariates used in the study:The *Strengths and Difficulties Questionnaire (SDQ)* [35–37] is a 25-item questionnaire that measures emotional problems, behavioral problems, hyperactivity, difficulties with peers, and prosocial behavior. Each item is rated on a 3-point scale (0 = “not true”, 1 = “sometimes true”, 2 = “certainly true”). The SDQ has a child/youth, parent, and teacher version. It also consists of an impact score that measures the degree of negative influence any problems have on different aspects of the child’s daily life (such as family activities and learning at school). Large population studies using the SDQ have been conducted in Norway [38, 39]. Regional norms for children and youth in Norway are available. The SDQ will be administered to children, parents, and teachers at the pre-intervention, post-intervention, and follow-up assessments.The *Social Skills Rating System (SSRS)* [40] is a standardized, multi-rater instrument that assesses social skills in children. It is administered to children, parents, and teachers. The children’s version has 34 items divided into four subscales: cooperation, assertion, empathy, and self-control. The parent scale includes 38 items measuring cooperation, self-esteem, responsibility, and self-control. The teacher’s version has 30 items assessing cooperation, self-esteem, and self-control. Each item is rated on a 4-point Likert scale, ranging from 1 (“never”) to 4 (“very often”). The SSRS has been used with Norwegian samples in earlier studies [41], and the teacher’s version has been validated and normed for children and adolescents in Norway [42]. The SSRS will be administered to children, parents, and teachers at the pre-intervention, post-intervention, and follow-up assessments*Five-to-Fifteen* [43] is a 181-item questionnaire developed to assess attention deficit hyperactivity disorder (ADHD), common comorbid conditions to ADHD, and associated problems in children and youth aged 5 to 17 years. The present study uses four subscales of the questionnaire with a total of 28 items which assess executive functions (attention and concentration, overactivity and impulsivity, passivity/inactivity, and planning/organizing). Items are rated on a 3-point scale (“does not apply”, “applies sometimes/to some extent”, “applies”) and are administered to parents and teachers at the pre-intervention, post-intervention, and follow-up assessments. The parent version of Five-to-Fifteen has been validated and normed with Nordic samples (Swedish, Danish, and Finnish) with acceptable psychometric properties [44]. The teacher version has been validated and normed in Danish samples with acceptable psychometric properties [45].*Demographics and background information.* Parents answer questions about their age, gender, marital status, pregnancy, ethnicity, education, occupation, living arrangements, income, relocation during the last 5 years, other children in the household, and whether they receive help from any health, care, or welfare service. Parents also answer questions about the child’s gender, age, and school grade, and if the child receives help from any other health, care, or welfare service. The child answers questions about his or her age and gender. Demographic information is collected at the pre-intervention, post-intervention, and follow-up-assessments. Background information about the family’s history of child welfare service (current and previous child welfare measures) is obtained from child welfare practitioners with parental consent.

### Procedures

#### Referral

Children and their families are referred to a child welfare agency by notification of concern (e.g., by teachers, community nurses, physicians, police, or others). The agency either opens a case of inspection or dismisses the note of concern. If probable concern is established, but not in terms of out-of-home placement recommendation, the family is offered support measures from CWS. If the family accepts, they are eligible for study inclusion if they fulfill the inclusion criteria.

#### Enrollment

At that point, a case worker at the child welfare agency reviews the family’s eligibility. If they are eligible, the case worker provides neutral information about the study and asks if the family is interested in participating. If they are interested, the case worker asks for oral consent to provide the research staff with the family’s contact information.

If consent is given, the research coordinator calls the parent and provides more information about the study and answers questions.

#### Consent

A home visit is scheduled to complete the recruitment and pre-assessments. A trained interviewer visits the family and provides detailed information about the study to both parents (if they are both present) and child. The interviewer reviews eligibility, verbal assent is collected from the child, and written, informed consent is collected from parents electronically on iPads. The parent is also asked to give consent to allow the child welfare practitioners to receive an oral summary of assessment results and for the research team to contact the child’s teacher. Consents and questionnaires are available in Norwegian, English, Arabic, and Somali.

#### Pre-assessment

Directly after consent, pre-assessments commence. The parent and child are each handed an iPad to answer questionnaires, and the interviewer administers the reading and math assessments on paper with the child. The pre-assessments take about 60 min to complete. After completion, an email with a link is sent to the child’s primary teacher providing information about the study, an invitation to answer questionnaires, and the secure online questionnaires. Within a week after pre-assessments, an oral summary of results from the assessments of reading and math skills, mental health, social skills, and executive functions is provided to the family’s assigned child welfare practitioner with the parent’s permission. The post-intervention and follow-up assessments are also conducted in home visits by an interviewer.

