### Aims and hypotheses

The present study has three overarching aims:To evaluate the feasibility of the IKT-K model designed to develop, implement, and evaluate empirically supported practice in CWSTo evaluate the effects of the intervention, EAS, on children in CWS and their familiesTo explore associations between implementation drivers (readiness, climate, fidelity) and outcomes for children and families.

The following research questions will be examined to evaluate Aim 1:To what degree are the core components of EAS implemented in the CWS?What adaptations are made to the core components of EAS?What are stakeholders’ perceptions of the IKT-K model’s feasibility and usefulness, as assessed in focus groups?To what degree are climate for implementing evidence-based practice (EBP) and susceptibility for change of practice (readiness for change) associated with intervention fidelity in the CWS?To what degree will practitioners in the experimental group increase their perceived competence in delivering academic support to children and families from pre- to post-intervention?To what degree is adherence to core components of EAS associated with academic achievement and parental involvement for families in the EAS group?

The following hypotheses will be tested to evaluate Aims 2 and 3:Children in families who receive the EAS intervention will improve their academic achievement relative to children and families in a parallel, active comparison group who receive “business as usual” (BAU) support.Parents who receive the EAS intervention will increase their engagement in their children’s school situation relative to parents who receive BAU.Intervention effects will be moderated by child age, readiness for change, and climate for implementing EBP.Covariates include children’s mental health, social skills, and executive functioning scores, as well as child gender and pre-intervention academic performance (math and reading) and parental involvement.Intervention effects (measured by academic performance tests and parental involvement) are associated with climate for implementing EBP and readiness for change.More adherence to EAS principles will be positively associated with academic achievement and parental involvement for families in the EAS group

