#### Randomization

At the time of consent, parents and children are informed that they will be randomly allocated to one of two conditions; one group, the BAU condition, receives regular measures from CWS, whereas the experimental condition receives the EAS intervention in addition to a regular child welfare measure. Blinding is not possible in this study; child welfare practitioners who have received EAS training will exclusively give EAS to study families, and parents and children will most likely understand to which group they have been assigned.

After completing the pre-assessment, participants are automatically randomized to either the intervention group (EAS) or the comparison group (BAU). A computer software (Confirmit) generates a random numbers table to assign random numbers to participants within blocks. A block randomization with a block of 10 is used, and randomization is carried out site-wise. The research coordinator informs the team manager at the site to assign the case to a practitioner with or without EAS training. All edit trails in Confirmit are recorded. Outcome assessors are blinded to allocation. In-depth technical details can be provided upon request.

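### Teacher forms counted as pre-intervention are requested only after the event that triggers randomisation, so they can be completed after allocation and, if late, after EAS has started

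*Protocol article*

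**What the plan says.** The Pre-assessment section describes a single home visit: parent and child questionnaires on iPads, and reading and math tests on paper. It states that "The pre-assessments take about 60 min to complete". The teacher comes in only afterwards: "After completion, an email with a link is sent to the child’s primary teacher". The email carries information about the study, an invitation and the online questionnaires.

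The Randomization section then states: "After completing the pre-assessment, participants are automatically randomized to either the intervention group (EAS) or the comparison group (BAU").

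The section on secondary measures and covariates places the teacher forms before the intervention. For the SDQ: "The SDQ will be administered to children, parents, and teachers at the pre-intervention, post-intervention, and follow-up assessments". For the SSRS: "The SSRS will be administered to children, parents, and teachers at the pre-intervention, post-intervention, and follow-up assessments". The Five-to-Fifteen items "are administered to parents and teachers at the pre-intervention, post-intervention, and follow-up assessments".

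On use, the Aims and hypotheses section says: "Covariates include children’s mental health, social skills, and executive functioning scores". The Statistical analyses section plans ANCOVA adjusted for baseline values and covariates, and lists Five-to-Fifteen among the variables for indirect effects. Neither section says which informant's score is meant.

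**The concern.** A covariate in an ANCOVA of a randomised trial should be fixed before treatment can influence it. The parent and child questionnaires and the academic tests meet that condition, because they are completed at the visit before allocation. The teacher forms need not. They are requested after the event that triggers allocation, and they are answered whenever the teacher gets to them.

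Two things could go wrong with a late form. If EAS has already changed the child's behaviour, adjusting for that rating removes part of the effect. If the teacher has learned the allocation, the rating may shift in either direction. EAS includes guidance to parents on involvement in school, and the Background section counts parent-teacher communication as part of such involvement, so a teacher might come to know. The blinding statement covers outcome assessors and does not mention teachers.

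At stake are the teacher-rated secondary contrasts and any model in which a teacher score is chosen as a covariate.

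**Working it through.** The article gives no figure to reproduce on this point. The check is first one of sequence, then an illustration of size.

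**Sequence**

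1. Home visit: consent, then directly the pre-assessment of about 60 minutes (Consent; Pre-assessment).
2. Completion of the pre-assessment triggers two things: the teacher email (Pre-assessment) and automatic randomisation (Randomization). The article does not order these two against each other, and neither waits for the teacher's reply.
3. The coordinator tells the team manager, who assigns a practitioner (Randomization). This seems to happen quickly, since the family's assigned practitioner is given the findings soon afterwards: "Within a week after pre-assessments, an oral summary of results".
4. EAS runs over 6 months, and assessment follows immediately after it (Methods and design). The post-assessment is 6 months after the pre-assessment (Post-assessment). EAS must therefore begin soon after allocation, although the date of the first session is not given.
5. A teacher reply delayed by some weeks can thus fall after allocation and within EAS, and would still count as pre-intervention.

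**Size, on assumptions**

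The ANCOVA effect is the arm difference in the outcome minus b times the arm difference in the covariate, where b is the within-arm slope. Let f be the share of teachers who reply after EAS has started, and s the shift in their ratings by then, in SD. Subscripts denote the arm.

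Change in the adjusted effect = −b × (f_EAS × s_EAS − f_BAU × s_BAU)

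The article gives none of these inputs. With the BAU term set to zero, f = 0.2 to 0.6 and s = 0.2 to 0.4:

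| b | Lower | Upper |
|---|---|---|
| 0.3 (academic outcome, only if a teacher score is a covariate) | 0.2 × 0.2 × 0.3 = 0.012 | 0.6 × 0.4 × 0.3 = 0.072 |
| 0.6 (same teacher scale as outcome) | 0.2 × 0.2 × 0.6 = 0.024 | 0.6 × 0.4 × 0.6 = 0.144 |

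A second parametrisation for a teacher-rated outcome lets g be the share of the final effect already present in a late rating. Then the share of the effect retained is 1 − b × f × g.

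- b = 0.5, f = 0.25, g = 0.25: 1 − 0.031 = 0.969, so a true d of 0.30 is estimated as 0.29.
- b = 0.7, f = 1, g = 0.5: 1 − 0.35 = 0.65, so a true d of 0.30 is estimated as 0.195, or about 0.20.
- f = 0: 1, no loss.

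The two are linked by s = g × final effect. With g = 0.5, s = 0.2 to 0.4 implies a final effect of 0.2/0.5 = 0.4 to 0.4/0.5 = 0.8 SD on a teacher-rated scale. The upper ends of the table are therefore generous.

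For scale, the unadjusted standard error of a standardised difference with 120 children in equal arms is 2/√120 = 0.18 SD.

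**The case against.** The case on the other side has several parts.

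- **Informant.** A reader might infer that teacher scores enter the primary ANCOVA. The article names constructs, not informants. SDQ and SSRS also come from child and parent, and Five-to-Fifteen also from the parent, all before allocation. Parent scores may already be the plan. This stands: teacher covariates in the primary models are possible, not stated.
- **Differential bias.** A reader might infer that only the EAS arm has anything to react to. The section on the comparison condition contradicts this: BAU may include academic support, typically by helping parents and teachers communicate. This stands, and setting the BAU term to zero is a simplification. A BAU shift in the same direction would reduce the net bias.
- **Timing.** A reader might infer that every teacher baseline is completed after randomisation. The article does not order the email against allocation, and it gives no reply dates. A form completed after allocation but before EAS starts, by a teacher who does not know the arm, does no harm. The first EAS session is for rapport and goals, so an early shift may be small. All of this stands.
- **Closing date.** A condensed article may leave a reply deadline to the full protocol. This stands, and the missing date is not the point. The point is the stated order combined with the pre-intervention label.
- **Randomisation may wait.** The teacher email sits under the Pre-assessment heading, so one could argue that allocation waits for the teacher. This does not stand. The email follows completion, and it is the participants who complete the pre-assessment and are then randomised automatically.

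**Conclusion.** The point holds in limited form. As written, the procedure lets teacher SDQ, SSRS and Five-to-Fifteen forms that count as baseline be completed after allocation and, for late replies, after EAS has started. Used as baseline for teacher-rated secondary outcomes, or as covariates if the teacher informant is chosen, such forms could bias the adjusted effect.

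The size cannot be derived from the article. The illustrative range for a teacher-rated outcome is 0.02 to 0.14 SD and rests wholly on assumed f, s and b with no shift in BAU. For an academic outcome it is 0.01 to 0.07 SD, and only if a teacher score is a covariate. All these values lie below the 0.18 SD standard error.

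It would go too far to conclude that the primary results are biased. The baselines of the reading test, the arithmetic test and PASS are taken at the home visit before allocation. This is a worthwhile, inexpensive safeguard rather than a threat to the main conclusions.

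**What to change.** 1. Count a teacher form as baseline only if its recorded completion time falls within one fixed window from the pre-assessment, applied identically in both arms and ending before EAS sessions begin. The article does not give the first-session date, so the window length should be set from the trial's own session timing, before any outcome data are examined. A cut-off tied to each family's first EAS session would not do, because BAU families have none and missingness would then differ by arm.
2. Treat later forms as missing baseline, under the multiple imputation already planned for the pre-post ANCOVA or the full information maximum likelihood planned for SEM.
3. Use the parent-rated SDQ, SSRS and Five-to-Fifteen, completed before randomisation, as the covariates in the ANCOVA of the primary outcomes, and say so.

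Sending the link at consent is not an effective remedy: consent and pre-assessment share one visit, so it gains only about an hour.

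The cost is modest. Some late teacher forms are lost as baseline and must be imputed, with some loss of precision for teacher-rated outcomes. Electronic data are collected in Confirmit and its edit trails are recorded, so completion times should be available. Recruitment was still in progress when the article was written, so the rule could be set before analysis.

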#### Randomization

At the time of consent, parents and children are informed that they will be randomly allocated to one of two conditions; one group, the BAU condition, receives regular measures from CWS, whereas the experimental condition receives the EAS intervention in addition to a regular child welfare measure. Blinding is not possible in this study; child welfare practitioners who have received EAS training will exclusively give EAS to study families, and parents and children will most likely understand to which group they have been assigned.

After completing the pre-assessment, participants are automatically randomized to either the intervention group (EAS) or the comparison group (BAU). A computer software (Confirmit) generates a random numbers table to assign random numbers to participants within blocks. A block randomization with a block of 10 is used, and randomization is carried out site-wise. The research coordinator informs the team manager at the site to assign the case to a practitioner with or without EAS training. All edit trails in Confirmit are recorded. Outcome assessors are blinded to allocation. In-depth technical details can be provided upon request.

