#### Power calculation

The study aims to recruit 120 families. The intervention under study is newly developed; hence, we used a meta-analysis testing the overall effect of similar interventions (targeting parental involvement in children’s learning, including “paired reading”) to inform the required sample size. The outcomes used to assess effect sizes in the meta-analysis were a combination of different standardized and unstandardized reading measures. The suggested effect sizes were in the range of *d* = .65 to 1.15 [22]. With α < 0.5, power = 0.80, and expected effect size *d* = .65, the necessary sample size is *n* = 78, with 39 families in each group. Although the Oral Reading Fluency (ORF) test administered in the current trial is similar to the assessments used by the studies in the meta-analysis, none of those studies used the actual ORF test of this trial. Hence, the power calculation lacks some precision. To account for uncertainty in the power calculation, subgroup analyses (of gender, site, and CWS measure), and possible study dropouts, and to compensate for the possibility of non-normal distribution of scores, more participants than deemed necessary according to the power calculation were recruited. Based on information from the participating CWS agencies about their target groups, this sample size seems attainable.

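### One stated block size of 10 per site in an open trial leaves up to one allocation in six deducible in advance by anyone holding the full site tally

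*Protocol article*

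**What the plan says.** All references are to the protocol article.

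- **Scheme.** Randomization: "A block randomization with a block of 10 is used, and randomization is carried out site-wise". No other block size is mentioned, and nothing says that sizes vary.
- **Ratio.** Randomization does not state it. The Power calculation section plans for equal groups, "with 39 families in each group".
- **Openness.** Randomization: "Blinding is not possible in this study". The same section says that outcome assessors are blinded and that EAS-trained practitioners will give study families only EAS.
- **Who learns the arm.** Randomization: "The research coordinator informs the team manager at the site to assign the case to a practitioner with or without EAS training".
- **Who approaches families.** Enrollment: "a case worker at the child welfare agency reviews the family’s eligibility", and, for eligible families, "the case worker provides neutral information about the study and asks if the family is interested in participating".
- **Timing of allocation.** Randomization: "After completing the pre-assessment, participants are automatically randomized". Between first approach and allocation come a call from the research coordinator, a home visit, consent and the baseline tests (Enrollment, Consent and Pre-assessment sections).
- **Publication.** Trial status: recruitment began in January 2018 and the trial was in progress when the article appeared.

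**The concern.** With one block size and a separate sequence at each site, the remaining places in a block are fixed once either arm has had its five families. In an open trial, anyone who has followed a site's allocations in order can then name the next arm. Here an agency manager is told each allocation, a case worker at the same agency makes the first approach, and the block size can be read in the article.

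Two safeguards in the article do not reach this step. Software allocation after baseline keeps the list itself hidden, but the first approach has already been made by then. Blinded assessors protect measurement, not the choice of whom to approach or when.

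The stake is selection bias. If a family thought likely to engage were approached when EAS was known to be next, the arms would differ in a way that the planned ANCOVA removes only as far as the measured baseline scores and covariates capture it. Parental involvement, one of the primary outcomes, is also reported by parents who will probably know their arm.

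**Working it through.** The article gives no predictability figure to reproduce. The only figure used is the equal split. A two-sided t-test at .05 (sidedness assumed) with d = 0.65, power 0.80 and equal groups needs 38.14 per group. Rounded up this is 39, with power 0.809, which matches the article and supports reading the blocks as 5:5.

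**Inputs**
- Block of 10 within each site (Randomization).
- Five EAS and five BAU per block (inferred, as above).
- 120 families at three agencies (Participants; Methods and design). 40 per site is an assumption; site sizes are not given.

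**Forced allocations, full tally, nobody pending.** There are C(10,5) = 252 equally likely blocks. Let F be the number of places at the end of the block that are forced because one arm is full. The number of blocks with F = k is 2·C(9−k, 4):

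| F | 1 | 2 | 3 | 4 | 5 |
|---|---|---|---|---|---|
| blocks | 140 | 70 | 30 | 10 | 2 |

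Mean F = (140×1 + 70×2 + 30×3 + 10×4 + 2×5)/252 = 420/252 = 1.667 per block. That is 1.667/10 = 16.7%, or 1 in 6, and 120/6 = 20 families if every block is filled. At least two places are forced in 112/252 = 44% of blocks. If a site's last block is incomplete, simulation gives 13.3%, 14.3% and 14.8% for sites of 25, 35 and 45 families.

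**Other families pending.** A prediction that could affect selection has to be made at the first approach. If L families at the site have been approached but not yet randomised, and will be randomised first, the observer's tally is L places behind. The certain share is then the mean of max(F−L, 0), divided by 10:

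- L = 1: (70×1 + 30×2 + 10×3 + 2×4)/252 = 168/252 = 0.667, so 6.7% (8 of 120)
- L = 2: (30×1 + 10×2 + 2×3)/252 = 56/252 = 0.222, so 2.2% (2.7 of 120)
- L = 3: (10×1 + 2×2)/252 = 14/252 = 0.056, so 0.6% (0.7 of 120)

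**Best guess.** Always guessing the arm with more places left in the block is right (5 + (4^5/252 − 1)/2)/10 = (5 + 1.532)/10 = 65.3% of the time, against 50% by chance.

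**Alternatives.** For a fixed block of 2m the certain share is 1/(m+1): 1/5 for blocks of 8, 1/4 for 6 and 1/3 for 4. A smaller fixed block would therefore be worse. For blocks drawn at random from 8, 10 and 12, a simulation of 40 families per site took an observer who holds the full tally with nobody pending and knows the set of sizes but not their order. About 1.5% of allocations were certain (1.8 of 120) and the best guess was right 64.5% of the time. The same program run with fixed blocks of 10 gave 16.6% and 65.3%, in line with the exact values.

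**The case against.** The strongest reply is that 1 in 6 is a ceiling that practice may never approach. It needs one person to know every allocation at the site in order, with no other family in the pipeline. The route from first approach to randomisation has several steps, so other families may well be pending. The article has the team manager informed and a case worker inviting, and nowhere says that they share a tally. Methods and design mentions teams, areas or units and several managers, so one manager may see only part of a site's sequence. Even an observer who knows where a block starts needs to have seen all five of one arm before anything is certain. All of this stands.

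A reader might infer that case workers choose whom to invite, or when, to suit the next arm. The article does not support that. Eligibility is reviewed once a family accepts support measures, the information given is to be neutral, and the interviewer checks eligibility again at the home visit. Nothing shows that selection has occurred or is intended.

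The reply does not go all the way. Practitioners, recruiters and champions meet bimonthly (Table 2), champions include managers and practitioners (Table 1), and their duties include following up recruiters (Knowledge translation procedure). These are channels by which a tally could travel, not evidence that it does. The article describes nothing to block them; the full protocol may.

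Timing is a further fair point. With completion estimated for December 2019 and a 12-month assessment, enrolment would have to end by about December 2018, so few families may remain to be randomised.

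**Conclusion.** The weakness is real but minor. A single published block size, run separately by site in an open trial, makes the end of each block deducible, and allocating after baseline does not prevent that. The size is up to 16.7% of allocations (at most about 20 of 120), falling to 6.7%, 2.2% and 0.6% with one, two or three families pending at the site.

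These figures assume 5:5 blocks, one constant block size and an observer with the complete site tally. The 16.7% also assumes that all blocks are filled. It would be tempting to conclude that site staff do know one allocation in six, or that the random list is exposed. The article supports neither: it does not show the tally reaching those who invite, and the list stays inside the software. The point is a cheap improvement, not a reason to doubt the allocations already made.

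**What to change.** For any families still to be randomised, set the software to block sizes that vary at random within each site, for example 8, 10 and 12. Start each site's new sequence when its current block of 10 is complete. Do not disclose the sizes or their order to site staff until recruitment ends. Do not simply shorten the fixed block.

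The gain is loss of certainty only: from 16.7% to about 1.5% certain if the set of sizes leaks, and less if it does not. The best-guess rate stays near 65%.

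The cost is one software setting and a possible imbalance at the end of recruitment of at most half a block, 6 families per site, against 5 under the present scheme. The benefit is small if recruitment is nearly complete. In that case the trial report can instead state who at each site knew the block size and the running tally, and compare baseline characteristics by position within block.
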